## **Endpoints**

The primary endpoint will be referable retinopathy

Secondary endpoints are referable maculopathy alone and referable retinopathy without maculopathy

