## **Inclusion criteria, entry and exit times**

The study will focus on the diabetes population aged 12 years and upwards since this is the group eligible for screening in national policy.

*Type 1 diabetes* : is defined by an algorithm that starts with the clinical assignment of type 1 in the clinical record but then excludes anyone with evidence of type 2 based on extensive oral prescription drug use or more than a year from diagnosis to insulin.

Type 2 diabetes: is defined by the clinical assignment of type 2 unless there is evidence to contradict this.

*Date of diagnosis*: this is taken from SCI-DM – in a small % of cases date of diagnosis is not known and earliest date known to have diabetes has to be used instead.

*Study start date*: 01/01/2007

*Study end date*: 01/06/2016

*Patient entry date* is defined as the latest of study start date, the date of diabetes diagnosis, and the date first evaluable for events (as defined below). Note that for the modelling purposes patient entry date will be further refined to be S2 day +1.

*Patient exit date* for a patient is the earliest of

- i) study end date,
- ii) the date of death,
- iii) the date last evaluable for events (as defined below)
- iv) or the date of the first event of interest.

Those who exit before an event or study end date are considered to be censored.

*Date first evaluable for events*

The dates from which individual patients are first considered evaluable for events are estimated from the dates of when either clinical measures (BMI, HbA1C and blood pressure [BP]) or drug prescription data are first available for that person, since these records confirm that a patient was in Scotland at the time and can therefore be considered evaluable for events.

*Date last evaluable for events*

The date last observable for events is defined as the earliest of

- i) the date last observable for routine data or drug data (i.e. exit from the country) whilst not under admission to hospital plus an additional 183 days
- ii) death, or 01/06/2016; Sensitivity analyses will evaluate the impact of this 183 day period which is in place so as not to censor people too early who simply haven't had any contact with clinical services during the period but who are still under observation.
- iii) *Date of suspension from screening for non eye disease related reason. Such patients can re-enter once the suspension has been lifted as evidenced by a further screening event*

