### *Event dates*

The date of the event will be taken as the date of screening on which referable retinopathy was detected. Each person time interval has a binary flag for whether an event occurred in a person-time interval.

We also have a censor date (which is the earliest of death/event/study end date/end of observability). If a person is censored and his event flag is 1, then that means he was censored because of the event. If at the person's last time-interval the event flag is 0, then he was censored for one of the other reasons (i.e. akin to a SURV object in R for Cox regression).

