### **Initial tabulations**

For each continuous covariate being considered :

- Summarise its distribution as mean median sd iqr and range and plot its distribution (density or histogram) plot
- Tabulate the frequency of all categorical variables

Events:

- Show the number (%) and event rate of incident events during follow up By AGE and SEX and diabetes type
- By Sex strata and for broad age bands and all ages combined show the age standardised event rate for each of the event of interest standardised to the 2013 European Standard Population

Then with any referable retinopathy as the event of interest :

- Summarise the distribution of follow up time range of person entry and exit dates
- Summarise the distribution of covariates at baseline by subsequent event status

- In the same table show the p value and the beta regression coefficient for the current age - sex -and diabetes duration -adjusted associations of all variables with the outcome

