## Model construction

*Assuming any referable retinopathy as event of interest initially:*

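### In the secondary-endpoint analyses the exit rule does not end follow-up when the other referable lesion is found, so patients with known referable disease stay in the risk set

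*SAP*

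**What the plan says.** The SAP's Endpoints section has two sentences. The first is "The primary endpoint will be referable retinopathy". The second is "Secondary endpoints are referable maculopathy alone and referable retinopathy without maculopathy". Neither secondary endpoint is defined further, and the section does not say whether the primary includes maculopathy.

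Under Inclusion criteria, entry and exit times, a patient leaves at the earliest of study end, death, the last evaluable date, "or the date of the first event of interest". Evaluability rests on routine clinical or drug records plus 183 days. It is also ended by "Date of suspension from screening for non eye disease related reason", with re-entry allowed at a later screen. Event dates repeats the rule: the censor date is the one "which is the earliest of death/event/study end date/end of observability".

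The event of interest is not the same throughout. Initial tabulations asks the analyst to "show the age standardised event rate for each of the event of interest", and Model construction opens with "Assuming any referable retinopathy as event of interest initially". The Objectives concern the first occurrence of referable retinopathy and the time until referable disease first appears.

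**The concern.** When maculopathy is the event of interest, referable retinopathy found earlier is not an event, a censoring reason or a reason to lose evaluability. The same holds with the lesions exchanged. A patient whose screening is suspended because of eye disease, but who still has HbA1c or prescription records, remains evaluable. The secondary risk set then mixes people free of referable disease with people already known to have it.

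This matters in two ways. If such a patient is not screened again, time can accrue in which no event can be recorded, because events are dated only at screening. If the patient is screened again, a second lesion may be counted as a new event. Neither gives the rate of a first referable lesion by type, which is what the objectives point to. The endpoint wording adds an ambiguity: a first referable screen showing both lesions may count as maculopathy or may belong to neither secondary endpoint. Two analysts following the SAP could report different rates.

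**Working it through.** The SAP states no lesion rate, event count or share of patients with both lesions, so there is no figure to reproduce. What follows is a range under assumptions.

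**From the SAP.** Study start 01/01/2007 and end 01/06/2016 are 3,439 days apart; 3,439 / 365.25 gives a maximum follow-up T = 9.42 years.

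**Assumed.** Constant total hazard λ of a first referable lesion, 0.5% to 5% per year. Share s of first referable screens with both lesions, 0 to 30%. The remainder is split 60:40, so the hazards are m = 0.6(1−s)λ (maculopathy only), r = 0.4(1−s)λ (retinopathy only) and b = sλ (both). There is no other censoring. The benchmark is the rate when everyone exits at the first referable lesion of any type.

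**Reading 1: *alone* means without referable retinopathy.**
- Mean person-time with exit at any lesion: PT = (1 − e^(−λT))/λ.
- Extra person-time if patients with the other finding, of hazard x, are kept to T: (x/λ)(T − PT).
- Rate relative to benchmark: PT / [PT + (x/λ)(T − PT)], with x = r + b for maculopathy and x = m + b for retinopathy.

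Example with λ = 0.03 and s = 0: PT = (1 − e^(−0.282))/0.03 = 8.20 and T − PT = 1.21. Maculopathy: 8.20/(8.20 + 0.4 × 1.21) = 0.944. Retinopathy: 8.20/(8.20 + 0.6 × 1.21) = 0.919.

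Here patients with both lesions fall in neither endpoint, so the two counts together are 1 − s of all first referable events: 90% at s = 10% and 70% at s = 30%.

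**Reading 2: maculopathy, with or without retinopathy, as its own endpoint.** Its hazard is M = m + b. Patients with retinopathy first stay at risk and later develop maculopathy at k times M, with k = 0, 1 or 3. Let S(t) be the share free of any referable lesion and R(t) the share with retinopathy first, where dR/dt = rS − kMR. The rate relative to M is then ∫(S + kR)dt / ∫(S + R)dt. This is below 1 for k = 0, exactly 1 for k = 1 and above 1 for k = 3. The retinopathy-without-maculopathy rate is diluted as in reading 1.

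**Results at T = 9.42 years** (ratio to benchmark; ranges over s and, for reading 2, k)

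| λ per year | Maculopathy, reading 1 | Retinopathy without maculopathy, both readings | Maculopathy, reading 2 | Component counts / all first events, reading 2 |
|---|---|---|---|---|
| 0.5% | 0.986–0.991 | 0.983–0.986 | 0.991–1.018 | 1.000–1.017 |
| 1% | 0.973–0.981 | 0.967–0.972 | 0.981–1.036 | 1.000–1.033 |
| 3% | 0.921–0.944 | 0.904–0.919 | 0.944–1.095 | 1.000–1.090 |
| 5% | 0.872–0.908 | 0.846–0.868 | 0.908–1.143 | 1.000–1.139 |

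With 5 years of follow-up, the reading 1 ratios lie between 0.91 and 0.995 over the same hazards.

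**The case against.** The strongest reply is that the intention is clear. The Objectives speak of first referable disease, and Event dates gives one event date, the screen at which referable retinopathy was found. Read together, they suggest that everyone leaves at that screen. As evidence of intent this stands. But the exit rule is tied to the event of interest, and Initial tabulations treats that as more than one event. The rule as written therefore does not deliver the intention in the secondary analyses.

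A second reply is that the effect is small. Modelled follow-up starts the day after the second screen, many patients enter after 2007, and the Data formatting example gives one row per later screen. On that layout a referred patient who is never screened again might add no further person-time. This also stands: the table assumes retention to 9.42 years for everyone and so shows the dilution near its greatest for each assumed hazard.

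A reader might go further and infer that patients with both lesions are omitted, that secondary rates are understated, and that components should add up to the primary. The SAP does not support these as facts. Omission follows only on reading 1; on reading 2 the two categories are complementary and nobody is lost at first detection. The direction is not fixed, because a later maculopathy counted as new raises that rate. Nor do the two faults generally occur together: on reading 1 a later second lesion makes the patient a both-lesion case, not countable unless the first lesion is no longer graded. The SAP nowhere promises additivity, which would also require the primary to include maculopathy.

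**Conclusion.** The point holds for the secondary endpoints. On either reading of *alone*, the written exit and censoring rules leave patients with known referable disease in the risk set, contrary to the stated interest in first referable disease. The bias can go either way for maculopathy; for retinopathy without maculopathy the model shows dilution only. Its true size cannot be computed from the SAP. Under constant hazards, a 60:40 split and retention to study end, person-time dilution is about 1 to 3% at 0.5 to 1% per year and about 9 to 15% at 5% per year. On reading 2 the maculopathy rate could lie anywhere from 9% below to 14% above the benchmark at the highest hazard. Shorter follow-up or loss of evaluability would shrink these figures.

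The classification of a first screen with both lesions is a separate ambiguity, whose effect depends on an unknown share. The primary exit rule, and the model that starts from any referable retinopathy, are not affected.

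**What to change.** In Inclusion criteria, entry and exit times, and in Event dates, state that for the primary and both secondary endpoints follow-up ends at the first screen showing any referable disease.

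In Endpoints, state whether the primary includes maculopathy, and classify that first screen into exclusive and exhaustive categories. Either use maculopathy only, retinopathy only and both, or use any maculopathy versus retinopathy without maculopathy. Report cause-specific rates for the chosen categories. If the primary includes maculopathy, these then sum to the primary rate.

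The cost is a few sentences, with the same data and the same kind of model. The drawback is that a separate category for both lesions may be small and imprecisely estimated; the two-category version avoids this.

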### **Baseline Covariates considered for inclusion in referable retinopathy prediction model**

The covariates to be considered for inclusion into the model are those reported in the literature as predicting retinopathy risk OR have been included in previous risk models.

Time updated covariates will be used in the analyses being updated wrt each screening date

- Sex coded
- Ethnicity
- Current age
- Age at diagnosis
- Pt entry date
- The Scottish Index of Multiple Deprivation (SIMD) quintile- this is a residence based measure of socioeconomic status .
  
- BMI (kg/m^2)
- Height, m
- HbA1c mmol/mol (To reduce potential for reverse causation, HbA1c values are to be lagged by at least one year. Start by considering running mean of readings taken between 1 and 3 years prior to baseline.)
- eGFR
- Albuminuria status ( 1: Normal 2: Micro 3: Macro)
  
- Systolic blood pressure, mmHg
- Diastolic blood pressure, mmHg
- Treated hypertension (based on prescription of any blood pressure lowering drugs)
  
- Total cholesterol, mmol/L
- Log (total/HDL) cholesterol
- Also consider non-HDL cholesterol, HDL-c and LDL-c as a set of lipid variables, choosing the combination giving the best model fit?
- Treated elevated cholesterol - ie on Statin therapy or other lipid lowering drugs (No LLT, statins, other LLT)
  
- Smoking status (categorised as never smoked, ever-smoked, current smoker- we do not think our pack year data are reliable enough to use pack years )
  
- Screening status at last screening available
  - We will also construct a weighted average of screening scores from all preceding episodes

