## **Data sources**

Scotland:

Anonymised data from a national clinical database of all patients with a READ code in their clinical record for diabetes mellitus (The Scottish Care Information – Diabetes Collaboration -SCI-DC/SCI-DM) system or more recently SCI-Diabetes). The assignment of such a diagnostic code triggers entry to the database. The most recently available data is the SCI-DM extract of May 2014 but this is currently being updated with data to late 2016.

SCI-DC data contain extensive info including all clinical measurements lab tests urine tests and issued prescriptions as well as annual retinopathy screening data. The data are linked anonymously to hospital admissions data (Scottish Morbidity Record SMR-01), held by the Information Services Division of the National Health Service (NHS) back to 1981, and death data held by the General Register Office for Scotland, using the CHI healthcare number with probabilistic linkage (mal-linkage rate <3%) [1].

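### Glucose-lowering treatment is not a candidate covariate, though prescriptions are held, so type 2 predicted risk may be off within treatment classes and the planned checks need not show it

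*SAP*

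**What the plan says.** The SAP's section on baseline covariates fixes the pool from which the prediction model is built. Its entry rule is that candidates are "those reported in the literature as predicting retinopathy risk OR have been included in previous risk models".

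- Two drug-treatment terms are on the list: "Treated hypertension (based on prescription of any blood pressure lowering drugs") and "Treated elevated cholesterol - ie on Statin therapy or other lipid lowering drugs (No LLT, statins, other LLT").
- Glycaemia is represented by HbA1c alone, and "HbA1c values are to be lagged by at least one year" to limit reverse causation. The starting point is a running mean of readings from 1 to 3 years before baseline.
- Insulin, non-insulin glucose-lowering drugs and diet-only management do not appear.

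The data for such a term are in hand. Data sources says that the database holds "all clinical measurements lab tests urine tests and issued prescriptions as well as annual retinopathy screening data". The type 1 definition, under Inclusion criteria, already draws on this kind of information: it "excludes anyone with evidence of type 2 based on extensive oral prescription drug use or more than a year from diagnosis to insulin".

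The Objectives call for separate type 1 and type 2 models. Under Model construction, the Poisson model starts from age, sex and diabetes duration and selects by backward elimination. The two-step analysis puts the hidden Markov score into a fuller model made of the covariates already described.

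**The concern.** The list treats three treatable risk factors differently. Blood pressure and lipids each have a measured value and a prescription-based treatment term. Glycaemia, in a model for a complication of diabetes, has only a measured value, and that value is at least a year old. Where the plan sets aside pack-years it says why; here it is silent.

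Backward elimination can only keep or drop what is listed, so no later step brings treatment in. Two type 2 patients with the same lagged HbA1c, age, duration, screening history and other listed values receive the same predicted risk, even if one is on insulin and the other on diet alone.

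This matters because the Utility assessment sets individual screening intervals from absolute risk, with 1%, 2.5% and 3% as example thresholds. If treatment class predicts referable disease beyond the other candidates, one class would be screened later than its true risk implies and another sooner. Performance evaluation plans a calibration plot, a calibration slope and a Hosmer-Lemeshow test, all pooled over treatment, and an AUROC averaged over age and sex strata. Errors of opposite sign by treatment class can cancel in all of the calibration checks.

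**Working it through.** **No plan figure to reproduce.** The SAP states no event count, treated share or effect size that bears on this point. The check therefore has two parts: a reading of the list, and an illustration on stated assumptions.

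**Reading of the list.**

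| Risk factor | Measured value listed | Treatment term listed |
|---|---|---|
| Blood pressure | systolic, diastolic | yes, from prescriptions |
| Lipids | total cholesterol, ratio, other fractions | yes, three levels |
| Glycaemia | HbA1c, lagged at least one year | none |

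**Illustration.** Take type 2 patients who share one pattern of listed covariates. Let

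- s = share on insulin (assumed 0.1 to 0.3);
- r = residual rate ratio, insulin versus not, given all the listed covariates (assumed 1.0 to 2.0);
- T = predicted risk. T = 2.5% is one of the SAP's example thresholds.

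A model without the treatment term predicts the average over the two groups, so

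- true risk on insulin = T × r / (1 + s(r − 1));
- true risk otherwise = T / (1 + s(r − 1)).

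Worked case, s = 0.2 and r = 1.5: the divisor is 1 + 0.2 × 0.5 = 1.10. On insulin, 2.5% × 1.5 / 1.10 = 3.41%. Otherwise, 2.5% / 1.10 = 2.27%. The average is 0.2 × 3.41% + 0.8 × 2.27% = 2.50%, which is why a pooled check can look sound.

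| r | On insulin, s = 0.1 / 0.2 / 0.3 | Otherwise, s = 0.1 / 0.2 / 0.3 |
|---|---|---|
| 1.0 | 2.50 / 2.50 / 2.50% | 2.50 / 2.50 / 2.50% |
| 1.25 | 3.05 / 2.98 / 2.91% | 2.44 / 2.38 / 2.33% |
| 1.5 | 3.57 / 3.41 / 3.26% | 2.38 / 2.27 / 2.17% |
| 2.0 | 4.55 / 4.17 / 3.85% | 2.27 / 2.08 / 1.92% |

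Applying the ratio on the hazard scale, 1 − (1 − T)^(ratio), changes little: at s = 0.2 and r = 2.0 it gives 4.13% in place of 4.17%.

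**Dependence on the independence assumption.** Using one s at every risk level assumes that treatment is unrelated to the other predictors. If insulin use is concentrated at higher risk, say an assumed s = 0.6 at the threshold with r = 1.5, the divisor is 1.30. The true risks become 2.5% × 1.5 / 1.30 = 2.88% on insulin and 2.5% / 1.30 = 1.92% otherwise. The error on insulin shrinks and the error in the others grows.

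**Discrimination.** A simulation of 2,000,000 rows assumed a mean event rate of 2% per interval, s = 0.2, and a standard deviation of 0.8 or 1.2 for the rest of the linear predictor. For r from 1.2 to 2.0, adding the treatment term raised the AUROC by between 0.0005 (0.8037 to 0.8042) and 0.013 (0.715 to 0.728).

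**The case against.** The strongest reply is that the omission breaks no rule of the plan. Candidates enter on literature evidence or use in earlier models, and the SAP alone cannot show that glucose-lowering treatment qualifies. Nor does the plan say why it lists the other two treatment terms, so the asymmetry is an observation and not a contradiction. This stands. It is met by asking the authors to add the term or give the reason for leaving it out.

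Second, other candidates may carry much of the treatment signal: duration, age at diagnosis, BMI, eGFR, albuminuria, past grades ("Screening status at last screening available" and a weighted history) and the hidden Markov score. This also stands. In the working, r is what remains after all of these, and it may be close to 1.

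Third, the formula holds for any omitted binary predictor, so the figures are not evidence about this one. That is correct: they show what a given r would imply and nothing more. The expected AUROC gain is small, and the SAP regards the AUROC as the most valid of its summary measures. The case therefore rests on calibration by treatment class.

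Fourth, the plan lags HbA1c because of reverse causation, and treatment at the screening date could raise the same question. The fix has to deal with that.

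A reader might go further and infer that the model will misplace the risk thresholds. The SAP does not support this. The thresholds are example policy values that no covariate can move, and harm to predicted risk needs a residual association that the document neither gives nor excludes.

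**Conclusion.** The point holds in a conditional form. The SAP lists treatment terms for blood pressure and lipids but none for glucose-lowering treatment, although it holds the data and already uses them to assign diabetes type, and it gives no reason. The type 2 model therefore has no term that distinguishes treatment classes among patients with the same listed values.

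Whether this harms prediction depends on the residual rate ratio. At 1 nothing is lost. At assumed ratios of 1.25 to 2.0 and insulin shares of 10% to 30%, with treatment independent of the other predictors, a predicted 2.5% would correspond to 2.91% to 4.55% on insulin and 1.92% to 2.44% otherwise. Average risk would be unchanged, and pooled calibration need not show the error. The direction, with insulin as the higher-risk class, is part of the assumption.

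The change is worth making before the models are fitted, because the data can then settle the question at little cost.

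**What to change.** 1. In the covariate section, add to the type 2 candidates a glucose-lowering treatment class from issued prescriptions (none; non-insulin only; any insulin). Update it at each screening, with the same age and sex interactions and the same elimination rule as the other candidates. If the authors prefer to leave it out, state why.
2. State whether the class is taken at the screening date or lagged like HbA1c, and run the other choice as a sensitivity analysis.
3. In Performance evaluation, report observed/expected events by treatment class for type 2 in the 30% test set.

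The cost is one categorical candidate (two parameters plus interactions), one sensitivity analysis and one table. No new data are needed. A deployed tool that keeps the term would have to read prescriptions, as it would for the blood pressure and lipid treatment terms. If the term is uninformative, the AIC rule can drop it.
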